**Table Tabb:** 

	Stage 1	Stage 2	Stage 3	Stage 4	Stage 5
Cumulative sample size per treatment arm reaching the respective stage	91	182	344	477	724
New samples per continued treatment arm and per stage	91	91	162	133	247
Overall cumulative sample size if no arm is dropped in any stage	273	546	1032	1431	2172

After each stage, an interim analysis will be done where non-inferiority of both arms is tested at the chosen stage-specific significance levels. Significant arms continue to the next stage, whereas non-significant arms can be dropped (non-binding). Together with the chosen stage-specific significance levels, the overall pairwise type 1 error rate (for the comparison of one experimental arm to control) equals 0.025 if stopping guidelines (i.e., for dropping of arms before the final stage) are ignored. If stopping guidelines are followed, 0.025 is an upper bound for the overall pairwise type 1 error rate.

The expected sample size for the design if all arms have an identical recurrence rate of 16.3% (implying non-inferiority of both experimental arms) and stopping guidelines are followed is 1928. If both experimental arms are inferior (with recurrence rates exceeding 16.3% by at least 7%, i.e., the non-inferiority margin) and stopping guidelines are respected, the expected sample size is 690.

Sample size calculations were done in STATA17.0 using nstagebin [6, 12]. The corresponding software output is shown in supplementary material A. Reanalysis of the meta-analysis was done in R [13] together with the package miceadds [14].

### Recruitment {15}

Expectations for the recruitment rate are based on the data from the first multicenter national study conducted by DACSUHS (DRAIN-TIME 1, ISRCTN 17021467) that terminated in April 2020. In this study, only patients who were able to give informed consent were enrolled. A total of 37 patients with CSDH were operated on per month in Denmark, and the study recruitment rate was 21 patients per month. It took 20 months to include the total number of 420 patients in DRAIN-TIME 1 (two arms). In contrast to DRAIN TIME 1, both capable and incapacitated patients are enrolled in this DRAIN-TIME 2 study. Depending on whether one of the drainage groups is excluded as a result of the interim analysis, the inclusion period will most likely be 2–4 years.

#### Assignment of interventions: allocation

##### Sequence generation {16a}

Participants will be randomly assigned to one of the three draining groups no later than 6 h postoperatively. Online randomization with a 1:1:1 allocation rate will be performed in each center using the REDCap randomize module in the REDCap database. Randomization is done separately in each center.

##### Concealment mechanism {16b}

Participants will be randomized using REDCap as described above. Allocation concealment will be ensured as the REDCap system will not release the randomization code until the patient has been recruited into the trial. This takes place after the medical history is taken and the clinical examination is performed. The drainage time group randomization is first released after the patient’s data and the signed consent form are uploaded to the database.

##### Implementation {16c}

All patients who give consent to participate and who fulfill the inclusion criteria will be randomized. Randomization will be performed by the on-call neurosurgeon who has operated on the patient and no later than 6 h postoperatively. The randomization result will be placed in a closed envelope.

Both in the medical record and on the envelope, the surgeon will state the time at which the envelope must be opened (6 h after the end of surgery for all patients). Identical information will be stated on the board by the patient’s bed. If the drain is to be removed after 12 or 24 h, the exact time of drain removal is written in the medical journal and on the board after the opening of the envelope (after 6 h of drainage). A member of the research team will continuously monitor whether this process is carried out correctly.

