#### Inclusion criteria

The following are the inclusion criteria:
Adult patients (≥ 18 years).Minimum 2 weeks’ time span from known head trauma.Patients with symptomatic CSDH confirmed on CT or magnetic resonance imaging (MRI), admitted to a neurosurgical department for operative treatment.Patients undergoing a single burr-hole evacuation and placement of a passive subdural drain.All patients independent of GCS at admission can be included.

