**Enrollment**					
**Eligibility screen**	X				
**Informed consent**	X				
***Randomization***	X				

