**Assessments**					
***Routine labs***	X		X		
***GCS***	X		X		
***mRS***	X		X		X
***Clinical examination***	X				
***SF-36***	X		X^#^		X
***Economic data***					X
***CSDH fluid****		X			
***CSDH membrane****		X			
***Blood****	X				

Schedule of assessments

*Ad* admission, *IO* intraoperative, *D* day, *mon* months, *GCS* Glasgow Coma Scale, *mRS* Modified Rankin Scale, *SF-36* Short Form (36) Health Survey

^*^Only collected in patients recruited to sub-study at Odense University Hospital and Rigshospitalet

^#^If not done the day of admission

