#### Assignment of interventions: blinding

##### Who will be blinded {17a}

Except for the on-call neurosurgeon who operates on the patient, everyone will be blinded to the randomization until 6 h post-surgery. The envelope will be opened by the nurse at exactly 6 h after surgery to determine whether the drain should be removed at that time or after 12 or 24 h. It is a passive drain, and the production rate cannot be affected by any external circumstances, which is why unblinding after 6 h is not considered an issue.

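### Table 2 puts randomisation at admission, the text puts it after surgery, and nothing ties release of the allocation to a completed, qualifying operation

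*Protocol article*

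**What the plan says.** The protocol article describes the moment of randomisation in several places.

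- Implementation {16c}: "Randomization will be performed by the on-call neurosurgeon who has operated on the patient and no later than 6 h postoperatively". The same section limits randomisation to consenting patients who meet the inclusion criteria, and has the surgeon write on the envelope an opening time counted from the end of surgery.
- Table 2 (Participant timeline {13}): the row "Randomization" has one mark, in the admission column. The row for drain placement has its mark in the next column, intraoperative.
- Sequence generation {16a}: "Participants will be randomly assigned to one of the three draining groups no later than 6 h postoperatively". This is an upper limit without a lower one.
- Concealment mechanism {16b}: the code is withheld until the patient has been recruited. On recruitment it says "This takes place after the medical history is taken and the clinical examination is performed", and then "The drainage time group randomization is first released after the patient’s data and the signed consent form are uploaded to the database".
- Data management {19}: online randomisation follows consent; surgery is not mentioned as a condition.
- The blinding section {17a} makes one exemption: "Except for the on-call neurosurgeon who operates on the patient, everyone will be blinded to the randomization until 6 h post-surgery".
- Inclusion criteria: "Patients undergoing a single burr-hole evacuation and placement of a passive subdural drain".
- Who will take informed consent? {26a}: consent may be taken on admission or directly after surgery.

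**The concern.** Table 2 and Implementation {16c} put randomisation on opposite sides of the operation. The difference matters for two reasons.

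First, the operating surgeon is the one person exempt from blinding during the first 6 h. If the allocation is drawn at admission, that surgeon evacuates the haematoma and places the drain knowing how long it will stay in. The protocol's argument that unblinding is harmless, because a passive drain's output cannot be influenced, is made for the period after 6 h. It does not cover knowledge of the arm before or during surgery.

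Second, one inclusion criterion describes the operation itself, so it is certain only once the operation is over. Patients randomised at admission may turn out to have a different procedure or no passive subdural drain. The trial is a non-inferiority trial analysed by intention to treat. Keeping such patients in the analysis adds people with no difference in drainage time and draws the arms together, which favours a non-inferiority conclusion. Removing them after the allocation is known would compromise the randomised comparison.

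**Working it through.** No stated figure depends on the time of randomisation, so the main check is a comparison of the sections.

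**1. Is the mark in Table 2 displaced by text extraction?** The randomisation mark is in column 1 of 5 (admission). The drain-placement mark is in column 2 of 5 (intraoperative), where it belongs. The column order survived, so the admission mark can be taken at face value.

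**2. Do the two sources agree?** Table 2: before surgery. Implementation {16c}: after surgery, since the randomiser has already operated. They do not agree.

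**3. Does another section settle it?**
- Sequence generation {16a}: only a latest time. Randomising at admission satisfies it.
- Concealment mechanism {16b}: history, clinical examination, data and signed consent are needed before release. Table 2 places the clinical examination at admission, and consent may be taken then. All the listed conditions can be met before surgery, and a finished operation is not among them.
- Data management {19}: randomisation after consent. The same holds.
- Who will be blinded {17a}: names the surgeon as unblinded without saying from when.

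A site could therefore randomise before surgery and comply with Table 2, {16a}, {16b} and {19}, while departing from {16c}.

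**4. What follows under each reading?**
- Table 2 followed: the surgeon can know the arm before operating, and the procedure criterion is still open at randomisation.
- {16c} followed: the operation is finished and the procedure known before the draw. Neither problem arises.

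**5. How large could the dilution be?** The documents give no share of patients randomised who then do not get the qualifying procedure. Call it f, an assumption, and suppose these patients have the same recurrence risk in every arm. Inputs from Sample size {14}: 724 per arm at the final stage, control recurrence 16.3%, margin 7 points, one-sided 0.025. The calculation uses the final-stage test only, on the risk-difference scale with a normal approximation.

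- Diluted excess: d = 0.07 × (1 − f). At f = 5%, d = 0.0665; at f = 10%, d = 0.063.
- Experimental-arm risk: pE = 0.163 + d, that is 0.2295 and 0.226.
- SE = √[(0.163 × 0.837 + pE(1 − pE)) / 724]. At f = 5%: √[(0.1364 + 0.1768)/724] = 0.0208. At f = 10%: √[(0.1364 + 0.1749)/724] = 0.0207.
- Chance of declaring non-inferiority when the undiluted excess equals the margin: Φ(−1.96 + (0.07 − d)/SE).
- f = 0: Φ(−1.96) = 2.5%.
- f = 5%: Φ(−1.96 + 0.0035/0.0208) = Φ(−1.79), about 3.7%.
- f = 10%: Φ(−1.96 + 0.007/0.0207) = Φ(−1.62), about 5.2%.

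These figures show direction and scale for an assumed f. They are not an estimate for this trial.

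**The case against.** The strongest reply is that the prose points to post-operative randomisation and one table mark does not outweigh it. The randomiser is someone who has operated, the envelope time is counted from the end of surgery, and proxy consent for incapacitated patients may come as late as 6 h after surgery, with randomisation following it. Only patients who meet the inclusion criteria are randomised, which, read with the first point, settles the procedure criterion beforehand. Concealment mechanism {16b} gives necessary conditions for release; it does not say that release happens as soon as they are met. Table 2 is coarse: it has no column between the operation and day 1, and it shows consent only at admission although the text also allows it after surgery.

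All of this stands. It makes a simplified table the likeliest explanation, but it does not remove the conflict: the table is part of the protocol, and no rule on release would stop a site that works from it.

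Some stronger readings are tempting but unsupported.
- A reader might infer that surgeons in this trial operate knowing the arm. The documents do not show that any site randomises before surgery, and they specify a standard operation. Bias from tailored surgery is possible only under the Table 2 reading, and cannot be quantified.
- A reader might infer that concealment at enrolment is broken. It is not: release follows consent and data entry.
- A reader might take 3.7% or 5.2% as the trial's error rate. Both rest on assumed fractions. Under {16c} the share with the wrong procedure should be close to zero.
- A reader might add patients whose endpoint occurs before 6 h. Their dilution arises under {16c} as well, so it does not measure this conflict.
- A reader might conclude that the surgeon should not draw the allocation at all. The protocol chooses this openly, and knowledge gained after surgery cannot alter an operation already done.

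**Conclusion.** The point holds as a contradiction with a conditional consequence. Table 2 and Implementation {16c} give different times of randomisation, and {16a}, {16b} and {19} leave the gap open because none sets an earliest time or requires a completed operation. The risk of a surgeon operating with knowledge of the arm, and of randomising patients whose procedure is not yet known, exists only where Table 2 is followed. The direction of the dilution is towards non-inferiority. Its size is unknown; the rise from 2.5% to about 3.7% or 5.2% assumes that 5% or 10% of each arm carries no contrast, with equal recurrence across arms in those patients, and considers the final-stage test alone. The correction is more than clerical, because a condition on release would determine what sites can do, but actual bias or error inflation is not demonstrated.

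**What to change.** Bring Table 2, Sequence generation {16a}, Concealment mechanism {16b} and Data management {19} into line with Implementation {16c}:

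1. State in each place that randomisation takes place after the end of surgery and no later than 6 h after it.
2. Show this in Table 2 by a 0–6 h post-surgery column or a footnote. Moving the mark under the existing post-surgery heading would not be enough, because that heading covers only day 1, day 2 and 3 months.
3. Make REDCap require three entries before the allocation is released: time of end of surgery, single burr hole performed, and passive subdural drain in place.

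Consent may still be taken at admission. The cost is a few required fields and a corrected table row, with no extra staff. Drawing the allocation nearer to 6 h, by someone other than the operating surgeon, is an optional further step that this point does not depend on; it would need someone on duty at that time with REDCap access.

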#### Assignment of interventions: blinding

##### Who will be blinded {17a}

Except for the on-call neurosurgeon who operates on the patient, everyone will be blinded to the randomization until 6 h post-surgery. The envelope will be opened by the nurse at exactly 6 h after surgery to determine whether the drain should be removed at that time or after 12 or 24 h. It is a passive drain, and the production rate cannot be affected by any external circumstances, which is why unblinding after 6 h is not considered an issue.

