### Data collection and management

#### Plans for assessment and collection of outcomes {18a}

##### Primary outcome

The overall primary clinical outcome is the recurrence of CSDH within 90 days after the initial surgery and drainage. Recurrence is defined as neurological deterioration leading to hospitalization, confirmed recurrent CSDH on cranial imaging (e.g., CT/MRI), and a need for repeat surgery. A retrospective review of the electronic medical record will be used to clarify whether the patient has experienced a recurrence.

Recurrence or no recurrence will be registered in REDCap by a member of the research team after 90 days.

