##### Secondary outcomes

A retrospective review of the electronic medical record will be used to clarify whether the patient has died during the observation period, and if so, for what reason.

The Modified Rankin Scale (mRS) is a clinician-reported measure of the patient’s degree of disability. It is widely applied for evaluating the outcome for stroke patients and as an endpoint in most randomized clinical trials [15]. It is a 7-level scale covering the entire range of functional outcomes from no symptoms to death. There is extensive evidence for the validity of the mRS, and the mRS categories correlate with the functional outcomes within the spectrum of stroke pathologies [16]. The limitations of the mRS are the subjective assignment of categories and the reproducibility of the score by examiners and patients [17]. A systematic review and meta-analysis of studies describing interobserver variability of the mRS reported pooled reliability (across 10 studies, *n* = 587 patients) of *κ* = 0.46 and a weighted *κ* of 0.90 [18]. To reduce interobserver variability, all members of the research group will be certified in the use of the mRS (http://rankinscale.org/).

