#### Plans to promote participant retention and complete follow-up {18b}

The time to follow-up is 90 days, which we believe is a sufficiently short follow-up period to minimize patient attrition and maximize the completeness of data collection. Most symptomatic recurrent CSDH cases related to the primary operation are expected to occur within this time frame [22]. The primary outcome data (CSDH recurrence at 90 days) will be obtained through the electronic medical record. To limit participant burden related to follow-up visits, we will contact each participant by phone after 90 days. Here, we will assist the patient in completing the SF-36 questionnaire (which they will have received via e-mail/E-boks) and determine the mRS category. If a member of the research team assesses that it is not possible to obtain a valid assessment over the telephone, the patient and their relatives are offered attendance at the outpatient clinic.

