### Oversight and monitoring

#### Composition of the coordinating center and trial steering committee {5d}

**Principal investigator:**
Preparation of protocol and revisionsPreparation of written patient informationApplying for ethical approvalOrganizing steering committee meetingsPublication of study reportsMember of steering committee DACSUHS

**Steering committee** (see title page for all members):
Agreement of final protocol.All investigators will be steering committee members; one lead investigator per department will be nominated as the local coordinator.Recruitment of patients.Reviewing the progress of the study and, if necessary, agreeing on changes to the protocol.Data verification.Randomization.

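### The reason given for accepting unblinding after 6 h covers drain output only; it does not cover the 90-day mRS, which can be masked cheaply, or the reoperation decision, which stays open

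*Protocol article*

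**What the plan says.** Under Who will be blinded {17a}, the Protocol article states that, apart from the operating neurosurgeon, "everyone will be blinded to the randomization until 6 h post-surgery". A nurse then opens the envelope. The section accepts open treatment from that point on one ground: "It is a passive drain, and the production rate cannot be affected by any external circumstances". It treats this ground as sufficient, concluding with the words "which is why unblinding after 6 h is not considered an issue".

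Implementation {16c} explains the exception: "Randomization will be performed by the on-call neurosurgeon who has operated on the patient". It also has the removal time entered in the patient's record and on the bedside board for the 12 h and 24 h arms. A research team member monitors this process.

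The outcomes are then obtained as follows.

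- **Recurrence** (Plans for assessment and collection of outcomes {18a}, Primary outcome) requires three things: deterioration with admission to hospital, imaging confirmation, and a need for reoperation. "A retrospective review of the electronic medical record will be used to clarify whether the patient has experienced a recurrence", and a research team member registers the result after 90 days.
- **mRS at 90 days** is scored by the research team, who telephone the patient to "determine the mRS category" ({18b}). On the scale itself, {18a} says "The limitations of the mRS are the subjective assignment of categories". It cites a pooled kappa of 0.46 and a weighted kappa of 0.90, and relies on certification to reduce differences between raters.

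The only blinding stated beyond 6 h is that of the biostatistician ({21a}), who assesses no outcome.

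**The concern.** The reason in {17a} answers whether knowing the arm could change how much the drain yields. It does not answer whether knowing the arm could change what is recorded as an outcome. Drain output is neither the primary nor a secondary outcome.

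Judgement enters at two points. One is the mRS category assigned at 90 days. The other is the surgeon's decision, at some time within the 90 days, that a deteriorating patient needs reoperation. The trial hypothesises that 6 and/or 12 h is non-inferior to 24 h. A higher reoperation threshold after short drainage would favour that conclusion, and a lower one would cost power. The mRS is tested for superiority (two-sided 0.05), and nothing stated protects it from rater expectation.

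**Working it through.** **Step 1. Who judges what, and what is said about masking.**

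| Step | When | Who | Room for judgement | Masking stated |
|---|---|---|---|---|
| Decision that reoperation is needed | On deterioration, within 90 days | Treating neurosurgeons | Yes, but anchored by hospital admission and imaging | None after 6 h |
| Registering recurrence | After 90 days | Research team member, from the record | Little; mainly abstraction | None |
| mRS | 90 days, by telephone | Research team member | Yes; called subjective in {18a} | None; certification addresses rater variability |
| Statistical analysis | Interim and final | Biostatistician | Not an outcome assessor | Blinded ({21a}) |

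That the 90-day assessor may know the arm is an inference. Blinding ends at 6 h for everyone. A removal time in the record identifies the 12 h and 24 h arms, and its absence points to 6 h. The research team monitors the envelope process and enters all data (Data management {19}). No sentence says that the caller knows the arm, and none prevents it.

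**Step 2. The plan's own figure.** Inputs from Sample size {14}: recurrence 16.3% in all arms, margin 7 percentage points, final one-sided alpha 0.025, final-stage power 0.95.

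n = (1.960 + 1.645)² × [2 × 0.163 × 0.837] / 0.07² = 12.995 × 0.27286 / 0.0049 ≈ 724 per arm, as stated.

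**Step 3. Sensitivity to a changed reoperation threshold.** Assumptions: one final look, 724 per arm, normal approximation on the risk difference, control at 16.3%, shift in the experimental arm only. The shifts are assumed, because the article gives none.

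P(claim) = Φ{ [0.07 − (pE − 0.163)] / SE − 1.960 }, with SE = √{ [0.163 × 0.837 + pE(1 − pE)] / 724 }.

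*Arm truly at the margin (23.3%, about 169 of 724), with a share of recurrences not counted:*

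| Share lost | Patients | Recorded pE | P(false claim) |
|---|---|---|---|
| 0 | 0 | 0.2330 | 0.025 |
| 5% | about 8 | 0.2214 | 0.081 |
| 10% | about 17 | 0.2097 | 0.206 |
| 15% | about 25 | 0.1981 | 0.409 |

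*Arms truly equal (16.3%), with recurrence over-called after short drainage:*

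| Excess | Recorded pE | Power |
|---|---|---|
| 0 | 0.1630 | 0.950 |
| 5% | 0.1712 | 0.884 |
| 10% | 0.1793 | 0.774 |
| 20% | 0.1956 | 0.459 |

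**Step 4. The same question under the five-stage design.** This was a simulation of 200,000 runs with risk-difference tests, the stage sizes as printed (91, 182, 344, 477, 724) and the stopping guidelines followed. Without bias it gives pairwise power 0.807 and familywise error 0.028, matching the stated 0.8 and 0.028.

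- If recorded recurrence in a truly inferior arm is 1, 2 or 3 points too low, pairwise error rises from 0.015 to 0.042, 0.104 or 0.211.
- If the arms are equal and recorded recurrence is 1, 2 or 3 points too high, pairwise power falls from 0.807 to 0.684, 0.527 or 0.358.

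No corresponding calculation is offered for the mRS, because the article gives no expected distribution.

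**The case against.** The case for the plan is substantial.

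- **Open treatment is largely inherent** when drain durations are compared, and the surgical decision cannot readily be masked. This stands.
- **Recurrence is not scored at day 90.** A reader might infer that staff who know the arm judge recurrence 90 days later. The article does not support that. Deterioration, admission, imaging and the reoperation decision all happen within the 90 days, and the later step mostly transcribes documented events. The open judgement is the surgeon's, made earlier.
- **Knowledge of the arm is inferred.** {5d} says "All investigators will be steering committee members", and that committee's tasks include recruiting and randomising. An overlap with the 90-day caller is therefore possible, but it is not stated.
- **The kappa of 0.46 should not be read alone.** The weighted value of 0.90 is in the same sentence and suits an ordered seven-level scale better. Neither value measures bias from knowing the arm. A clinic visit is offered when the telephone assessment is not valid, but that concerns validity and not masking.
- **The error and power figures model a shifted reoperation threshold.** Masking the telephone call and the record entry would not remove that.
- **This is a condensed article**, and assessor logistics may be in a fuller document. That would excuse silence. It does not excuse a stated justification that leaves outcome assessment out.

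**Conclusion.** The point holds in a limited form. The reasoning in {17a} is incomplete because it dismisses unblinding on a ground unrelated to outcome assessment. The clearest consequence is for a secondary outcome: the 90-day mRS is a subjective rating with no stated protection from knowledge of the arm. For the primary endpoint, the exposure lies in the reoperation decision during follow-up. Hospital admission and imaging criteria limit it but do not remove it.

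The direction and size of any bias are unknown. A reader might take the rise from 2.5% to 8%, 21% or 41% as the trial's expected false-claim rate, or as what masking would save. It is neither. These figures rest on assumed one-sided shifts and a single final look, and they show only how sensitive the conclusion is to the reoperation threshold. This is a low-cost improvement and not a defect that invalidates the design.

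**What to change.** 1. In {17a}, delete the claim and state plainly that treatment is open after 6 h.
2. Have the 90-day call and mRS scoring done by an existing certified team member who was not involved in that patient's inpatient care, with allocation and drain removal time hidden by REDCap user rights.
3. Hide the same fields from the person registering recurrence, as far as the record allows.
4. Add one field to the 90-day entry: neurological deterioration with imaging-confirmed recurrence, whether or not reoperation was judged needed. Report it by arm as a supportive endpoint beside the primary one, so that a difference in reoperation threshold between arms can be seen.

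The cost is a rights setting, a call-rota rule at each department and one extra field. The sample size and visits do not change. The limits should be stated too. Each department needs a suitable second person for the call. Patients may disclose their drainage time, and the record under review may reveal the arm. Decisions to readmit, scan and reoperate remain open, so item 4 can expose a shifted threshold but cannot prevent one.
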